## Abstract

**Background:**

Medical students experience high rates of burnout and mental health distress, with approximately half reporting burnout, one-third experiencing depression, and one-tenth having suicidal thoughts. These issues are exacerbated during clinical placements and contribute to workforce attrition after qualification. Existing interventions are largely generic and show limited effectiveness. Thumos, a cognitive-behavioural therapy-based intervention specifically tailored for healthcare professionals and medical students, addresses the stressful situations intrinsic to medical training and practice. This randomised controlled trial will evaluate whether Thumos improves psychological resilience, confidence in dealing with stressful situations, burnout, and depression in medical students compared with services as usual (SAU).

**Methods/design:**

Two hundred and twenty UK medical students in a year that contains a clinical placement of a week or longer will be recruited nationally from UK medical schools. Participants will be randomised 1:1 to receive either Thumos (two online group workshops and one individual video/phone call) or SAU. Assessments will occur at baseline, post-intervention, 4-month, and 9-month follow-up. The primary outcome is psychological resilience measured by the Brief Resilience Scale at 4-month follow-up. A mixed-methods process evaluation will assess acceptability and feasibility.

**Discussion:**

To our knowledge, this is the first randomised controlled trial of an intervention specifically designed to prepare medical students for stressful clinical events. If effective, Thumos could potentially be adapted for medical students in other countries.

**Trial identifier and registry name:**

ISRCTN12744098: https://www.isrctn.com/ISRCTN12744098; An evaluation of a cognitive-behavioural intervention for medical students

## Introduction

Healthcare systems internationally are experiencing a workforce crisis, with a current global shortage of six million physicians [1]. While poor workforce planning has contributed to this problem, high turnover has been identified as the main contributing factor [2]. Inadequate staffing is linked with negative patient outcomes including extended hospital stays and mortality [3]. It also creates a vicious cycle, whereby existing staff become overworked and burnt-out, a syndrome characterised by exhaustion and disengagement [4]. Higher burnout then increases the risk of sickness absence and turnover, further exacerbating staffing shortages [5,6] and directly leading to the delivery of poorer patient care [7].

In a review of 170 studies in doctors, higher burnout was associated with twice the risk of patient safety incidents and a two-fold reduction in patient satisfaction [7]. Within this vicious cycle, provider burnout and poor well-being must be recognised as an active component, serving to drive the workforce crisis. Equally, addressing this component by better supporting healthcare professionals could help to break this cycle, leading to reduced sickness absence, better retention, and better patient care [8].

Most burnout research has focused on qualified professional groups, but there is a growing recognition that it could be beneficial to intervene during training, prior to professional registration, due to high rates of mental health distress in these cohorts [9]. Studies in medical students indicate half report burnout, one in three report depression and one in ten experience suicidal thoughts [10–12]. Furthermore, the immediate post-qualification years have been recognised as a high-risk time for physicians leaving the profession [13]. Poor mental health and burnout are linked with higher attrition [14], so improving their mental well-being could be one way to enhance retention and reduce physician shortages.

Multiple risk factors unique to medical training have been implicated in these mental health difficulties, notably demanding academic requirements and perfectionism-related cognitive patterns [15,16] and exposure to stressful clinical events on placement [17]. Indeed, rates of burnout in medical students increase significantly during the years involving clinical placements [18]. However, there has been a lack of interventions tailored for medical students and none which prepare medical students for stressful workplace events [19]. Previous evaluations of mental health support for medical students have predominantly examined non-tailored approaches such as mindfulness-based programmes, relaxation techniques, and yoga [19]. Evidence for these interventions is weak and mixed, and they have been criticised for lacking relevance [20]. A recent meta-analysis of resilience interventions for medical students indicated that these interventions are moderately effective at reducing stress and mildly effective at increasing resilience within medical students [21]. The implication that these interventions may have more favourable impacts on stress suggests that further research is required to examine the specific factors that influence resilience. There is an urgent need for effective, preventative interventions which help students cope with the specific occupational stressors they will encounter during their placements, training, and beyond.

The current trial will evaluate Thumos, an intervention that employs cognitive-behavioural therapy (CBT) techniques to prepare healthcare professionals and students to manage stressful work or training events. Thumos is based on the principles of Reboot (Recovery-boosting), an approach that has been investigated, tested and developed in several studies previously [9,22–26]. The approach used in Thumos differs from many previously evaluated psychological interventions for medical students in three ways. Firstly, it has been designed with healthcare professionals in mind, based upon a combination of 1) research into the effects of patient safety incidents and other work stressors, 2) resilience theory, and 3) CBT techniques. Secondly, Thumos integrates complementary therapeutic formats: group sessions that facilitate peer connection, alongside an individual consultation that provides personalised support. Thirdly, Thumos addresses the stressful situations that are intrinsic to healthcare work, providing support for those unavoidable events that cannot be improved through organisational interventions.

Characteristics of Thumos may make it particularly well suited for medical students. For example, the preventive framing of the intervention may help address barriers related to help-seeking stigma, which research has identified as a significant obstacle to engagement with mental health support among medical students [20,27]. It also uses case studies and materials which are tailored towards the stressful experiences medical students may face on placements. This approach increases the sense of relevance of the intervention for participants which may increase engagement [9]. Furthermore, it directly addresses unhelpful perfectionist thinking styles that have been associated with psychological distress in this population [16].

There have been three uncontrolled evaluations of versions of Reboot, the CBT-based intervention on whose principles Thumos is based, which indicate positive findings. The first was in a group of 66 multi-disciplinary healthcare professionals and students; results indicated it was associated with improvements in participants’ confidence, coping knowledge and psychological resilience [22,23]. The second was in 80 Critical Care Nurses (CCNs) [24,25]. Participation was associated with increased confidence and resilience and reduced depression and burnout. Nurses also reported a lower intention to leave clinical practice following the intervention [24]. The third evaluation was in 115 medical students [9]. Findings indicated the intervention was feasible and potentially effective in this group, with participants reporting significant increases in resilience and confidence in coping with adverse events, and significant decreases in burnout and depression [9]. Qualitative findings from these evaluations indicate that participants appreciate the intervention’s tailored format and opportunity for peer support alongside professional input. They describe increased self-awareness and report the acquisition of psychological skills which they could apply to cope with work stressors [22–26].

Feedback from these evaluations was used to make improvements to, and to further tailor, Reboot towards medical students, including new exercises, reduction of didactic information and changing the phone call discussion. There is now a need to test this refined intervention, Thumos, and to ascertain whether observed improvements in outcome indicators can be attributed to the intervention. This study addresses this gap, through a definitive randomised controlled trial (RCT). The comparator intervention is Services as Usual (SAU); this comparison will establish whether and what benefits Thumos may offer above what is currently available. The final follow-up time point is 9 months and create the possibility of conducting a subsequent 5-year follow-up study, should initial results be positive.

## Aims and objectives

The main purpose of the trial is to establish whether Thumos increases resilience and improves mental health in medical students.

The primary objective is:

To determine whether Thumos is superior to the control condition (services as usual; SAU) at 4-month follow-up in increasing psychological resilience in medical students.

Secondary objectives are:

1. To determine whether Thumos is superior to SAU at 9-month follow-up in increasing psychological resilience.2. To determine whether Thumos is superior to SAU at 4-month and 9-month follow-ups in the endpoints of confidence, burnout, depression, mental health, and self-reported sickness absence.3. To assess acceptability and how Thumos is delivered in practice through a process evaluation with users, medical educators, and providers

## Materials and Methods

### Trial design

This study is a randomised controlled parallel groups intervention trial (see S1 CONSORT Checklist in S1 File). All United Kingdom (UK) medical schools will be invited to participate (see S3 Appendix 1 in S3 File). Participants will be self-selecting and screened for eligibility based on the criteria that they are a) UK medical student and b) in a year of study that contains a placement of one week or longer. The trial will compare Thumos to a control condition of services as usual (SAU), where medical students in either condition can continue to access available mental health support as they usually would. Data collection will occur at four time-points, Time 1 (T1), pre-intervention (baseline); Time 2 (T2), post-intervention (following completion of Thumos/6 weeks after baseline for control group); Time 3 (T3), 4 months following baseline and Time 4 (T4), 9 month following baseline (see Fig 1). All elements will be conducted online, with questionnaires administered via Qualtrics and interviews/intervention sessions via online video platform. Participants will be contacted to complete the post-baseline measures via Qualtrics using email as the first point of contact and subsequent attempts to contact will be via SMS or email. All participants that complete post-baseline measures will be awarded a £10 shopping voucher per survey as compensation. Informed consent will also be taken online, with participants asked to read the information sheet and provide written informed consent via Qualtrics prior to responding to any data collection items (see S4 Appendix 2 in S4 File). A process evaluation will include medical student participants, medical educators from medical schools of participating students and the Thumos therapists.

**Fig 1 pone.0355371.g001:**
[figure not shown]
SPIRIT schedule of enrolment, interventions, and assessments.

### Randomisation and Blinding

Randomisation will be undertaken following completion of baseline assessments using the web-based Sealed Envelope software. Randomisation will be in the ratio 1:1 to the two groups. *The statistician will conduct the primary analysis using masked treatment labels, with allocation revealed only after the primary dataset is locked and the masked primary results have been checked, as described under Statistical Analysis*. The CBT therapists, researchers and participants will be unblinded.

### Study population for randomised controlled trial

#### Inclusion criteria.

UK medical students in years involving clinical placements of a week or longer nationally. We will recruit from these groups to the main trial until recruitment numbers are saturated.

### Exclusion criteria

Medical students based in a medical school outside of the UK or students in a year without a clinical placement of a week or longer. Recruitment will end once we have reached our maximum number of participants to recruit (n = 220) and exclude all prospective participants at this time.

### Study population for process evaluation

#### Inclusion criteria.

Participating medical students: We will recruit medical students in the main trial to also take part in the process evaluation. Both control and intervention arm students will be invited to complete process questionnaires; only intervention arm medical students will be invited to take part in qualitative interviews.

UK medical educators: We will recruit medical educators in schools with participating students within the intervention arm to qualitative interviews as part of the process evaluation.

The cognitive behavioural therapists/clinical psychologists delivering the intervention will be invited to qualitative interviews as part of the process evaluation.

### Exclusion criteria

Medical students: We will exclude those who did not complete the intervention from the qualitative interviews.

UK Medical educators: We will exclude those from medical schools without participating intervention arm students. For the qualitative interviews, we will stop recruiting once we have reached data saturation, defined as ‘information redundancy’ where no new information or value is generated from the data.

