### Process evaluation outcomes

**To assess acceptability and how Thumos is delivered in practice through a process evaluation with users, medical educators, and providers.**

We drew upon UK Medical Research Council (MRC) guidance for process evaluations of complex interventions [36] to design a mixed-methods approach to the process evaluation.

Psychological therapist logs: Weekly logs will assess therapists’ experiences of intervention delivery, including perceived benefits, mechanisms, and challenges.Process questionnaires: Process questionnaires at T2 (post-intervention) will explore participants’ reasons for participating, and their perceptions and experiences [37]. Participants in the intervention arm will be asked about their affective attitudes to the intervention, general acceptability, perceived effectiveness, ethicality, intervention coherence and mechanisms, self-efficacy, burdens, opportunity costs, and barriers and facilitators. Participants in the control arm will be asked about their reasons for participating, and their perceptions and experiences of the study.Field notes: Researchers’ field notes will track any changes in the delivery of the intervention; enabling recording of protocol changes.Participant interviews: At T3, a randomly selected subset of participants from the intervention arm will be invited to 30-minute semi-structured interviews (n = 20) to generate information regarding intervention delivery, feasibility and acceptance, and barriers and facilitators to participation.Medical educator interviews: Once all experimental participants have completed T2 data collection, medical educators (n = 15) at schools where students have participated in the study will be interviewed to explore 1) their perceptions of the research process, and 2) perceived benefits or drawbacks of Thumos at an organisational level, 3) ways Thumos could be implemented at scale for medical students.Therapist interviews: Once all experimental participants have completed T2 data collection, all trial therapists will be invited to 30-minute semi-structured interviews exploring their experiences of delivering the intervention.

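### Students who did not complete Thumos are excluded from the interviews meant to inform acceptance and barriers to participation, so the student interview findings will come from completers only

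*Protocol article*

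**What the plan says.** The third secondary objective (Aims and objectives) is "To assess acceptability and how Thumos is delivered in practice through a process evaluation with users, medical educators, and providers".

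The student part of the process evaluation has two strands.

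- **Interviews.** Under Study population for process evaluation, the inclusion criteria state that "only intervention arm medical students will be invited to take part in qualitative interviews". The exclusion criteria that follow add: "We will exclude those who did not complete the intervention from the qualitative interviews". Under Process evaluation outcomes, the sample is described differently: at T3, "a randomly selected subset of participants from the intervention arm will be invited to 30-minute semi-structured interviews", with n = 20. Their purpose is "to generate information regarding intervention delivery, feasibility and acceptance, and barriers and facilitators to participation".
- **Questionnaires at T2.** The inclusion criteria state: "Both control and intervention arm students will be invited to complete process questionnaires". No completion requirement is given. On content, "Participants in the intervention arm will be asked about their affective attitudes to the intervention, general acceptability, perceived effectiveness", and the list continues to "burdens, opportunity costs, and barriers and facilitators".

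Therapist logs, field notes, educator interviews and therapist interviews complete the sources.

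**The concern.** Acceptability and barriers are the topics on which completers and non-completers are most likely to differ. A student who finished the programme has, by definition, overcome whatever barriers arose. A student who stopped may have met one that was not overcome. Restricting the interviews to completers selects the sample on something close to the quantity being studied, and the likely direction is favourable to Thumos.

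Two things are at stake. First, if adherence turns out low, or the primary comparison is null, the interviews cannot help to explain why students stopped. The plan allows for non-adherence: the Statistical Analysis section defines minimum adherence and builds per protocol and complier average causal effect analyses on it. Second, the Discussion says that the results should help relevant bodies decide whether to invest in provision. Interview themes drawn only from completers could be read as the view of everyone offered the programme, especially since the section describing the interviews calls the sample random within the intervention arm.

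**Working it through.** The article states no figure to reproduce, so the check sets the passages side by side.

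1. **Purpose against eligibility.** Process evaluation outcomes gives the interviews the task of informing acceptance and barriers to participation. The exclusion criteria remove every student who did not complete. The number of non-completers among the 20 interviewees is therefore zero by rule, whatever the non-completion rate. The rule works against the stated purpose.

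2. **Sampling description against eligibility.** Process evaluation outcomes describes random selection from the intervention arm; the exclusion criteria narrow the frame to completers. Both can be satisfied by drawing at random among eligible completers, so this is not a strict contradiction. But a reader of Process evaluation outcomes alone would take the 20 to represent the whole arm.

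3. **Meaning of completion.** The article does not define completion for the interview rule. The nearest definition is minimum adherence (Statistical Analysis): both workshops within six weeks of randomisation, at least 75% attendance at each, individual call not required. A student who attended both workshops but missed the call could be classed either way. The detailed protocol, which is not shown, may settle this.

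4. **Whether other sources fill the gap.**
   - The T2 questionnaire goes to both arms and asks the intervention arm about acceptability, burdens and barriers. It covers the topics. In the integration described under Statistical Analysis it enters as survey scores and frequencies, not as interview accounts. The Trial design section times T2 in the Thumos arm by completion of the programme, so the article leaves unclear when a non-completer receives it.
   - Therapist logs, field notes, and therapist and educator interviews are second-hand on why a student stopped.
   - The stated reasons for non-response in the Statistical Analysis section concern missing outcome data, not stopping the intervention.
   
   Coverage is therefore partial. None of these sources is a first-hand interview with a student who stopped.

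5. **Consequence for integration.** The joint display will set questionnaire results, which may include non-completers, beside student interview themes that cannot. Divergence between the two could then reflect who was asked rather than what was asked. The Limitations section covers self-selection into the trial but not this selection within it.

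6. **Why no bias figure is given.** The article states no non-completion rate. The 30% for Thumos in the Sample size calculation is dropout by T4 and should not be read as non-completion of the programme. The interviews are analysed by reflexive thematic analysis, which identifies themes and does not estimate the proportion who find Thumos acceptable. A percentage bias would have invented inputs and no matching estimand.

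**The case against.** The strongest case on the other side is that interviews are only one strand. The exclusion applies to the interviews alone; the questionnaire reaches students in both arms without a stated completion requirement and asks about the very topics said to be lost. Timing T2 by completion says when the survey falls, not who may answer it. Table 3 labels T2 as post-intervention or an equivalent time, and the primary model uses T2 data from participants analysed as randomised, so responses from non-adherent students are expected. Interviewing people who received the full programme is also defensible when delivery and content are among the topics. Nothing here touches randomisation, the primary outcome or any efficacy estimate.

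Most of this stands, and it sets the limits of the point. A reader might infer that the whole process evaluation hears only completers, that the third objective cannot be answered, or that low adherence or a null result would be left wholly unexplained. The documents support none of these. The questionnaire covers acceptability and barriers, educators and therapists are heard, fidelity is monitored, adherence is summarised and analysed, students who miss sessions are contacted, and those reporting strong dislike or discomfort are followed up under Safety Reporting.

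What the objection does not remove is the mismatch between the interviews' stated purpose and who may be interviewed. Interest in delivery and content justifies including completers; it does not justify excluding everyone else when barriers to participation are also a stated topic.

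**Conclusion.** The point holds for the student interviews. Their findings will come from completers only and are likely to be favourably selected on acceptability and barriers, and no planned source gives interview accounts from students who stopped. The other sources compensate in part. The third objective remains answerable, but with a gap where explanation of non-completion would be most useful.

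The direction of selection rests on the assumption that students who stopped tend, on average, to be less favourable or to have met more barriers than those who finished. That is plausible but not shown in the article. The size cannot be stated, for the reasons above. The efficacy analyses are unaffected. The change is worth making because it is cheap and addresses a stated purpose of the interviews.

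**What to change.** - Remove the exclusion of non-completers from the student interviews.
- Within the same total of about 20 interviews, or those still to be done, purposively include some students who did not meet the stated minimum adherence definition, and ask their reasons for stopping. The documents give no basis for a particular split, so the number is for the study team to set and report.
- Align the exclusion criteria with the description under Process evaluation outcomes, so that both state the same sampling frame and use the same definition of completion.
- If the exclusion is kept, state in the methods and the limitations that interview findings apply to completers only.

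**Cost.** A minor amendment and slightly fewer completer interviews. Non-completers are harder to reach, although the Intervention section already provides for contacting those who miss sessions by email, text and telephone. Timing also limits what can be done. Recruitment began on 16 June 2025 and interviews take place at T3, nominally four months after baseline, so the first could have fallen from about mid-October 2025 (June plus four months), before the protocol version of January 2026. Some may already have been done. With recruitment expected to end on 31 March 2026, the last nominal T3 falls around the end of July 2026 (March plus four months), so later participants could still be included.
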